## Abstract

**Background:**

Nicotine addiction among youth is a continuing public health concern, and vaping serves as a major pathway to nicotine use. Conventional assessments of craving and addiction risk rely on self-reports, which are prone to bias and lack sensitivity to real-time processes. Virtual reality (VR) enables controlled cue exposure while capturing real-time multimodal data, including subjective experiences, behavioral patterns, and physiological responses, which offer a more implicit and dynamic approach to identifying addiction risk.

**Objective:**

This pilot study examines whether subjective craving and psychophysiological responses (eg, eye gaze, heart rate, and electrodermal activity) to vaping-related cues in VR can distinguish young adults who vape from those who do not. Our secondary objective is to explore associations between these multimodal biomarkers and self-reported measures of craving, dependence, motivation to quit, and susceptibility to initiate vaping.

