This study addresses these critical gaps by evaluating whether psychophysiological responses to vaping cues in VR can differentiate nicotine vaping status among young adults. It also explores the associations between biometric reactivity, nicotine vaping status and intention, and individuals’ addiction-related traits (eg, impulsivity and emotion regulation). The long-term goal is to inform the development of real-time adaptive systems capable of detecting and predicting vaping-related intentions, addiction, and initiation risk in naturalistic VR settings, and delivering tailored behavioral-change interventions. This will support the development of early, personalized prevention strategies to enhance health outcomes among youth.

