#### Primary Aim

The primary aim is to examine differences in psychological (craving, sense of presence, and social presence) and physiological (eye gaze, HR, and EDA) responses between young adults who currently vape and those who have never vaped during exposure to VR vaping cues presented with and without social pressure. We hypothesize that vapers will exhibit stronger craving, a greater sense of presence and social presence, increased visual attention to vaping cues, and heightened physiological arousal compared with nonvapers across both VR scenes. We further expect that both groups will show stronger psychological and physiological responses in the social pressure condition than in the no pressure condition.

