## Methods

### Study Design

This study will examine individuals’ psychological, behavioral, and physiological responses to e-cigarette cues in VR among young adults aged 18 to 21 years. We focus on this age range because the transition into early adulthood often brings increased exposure to vaping-related social contexts (eg, college gatherings) [27], and this pilot allows us to first test the paradigm in adults before adapting it for adolescent populations. A between-subjects design is used to compare current e-cigarette users and nonusers, with a within-subject, counterbalanced component to assess 2 cue conditions (with and without social pressure). This mixed-design approach enables testing of cue effects and group differences while controlling for individual variability.

Prior VR nicotine cue reactivity studies have reported medium-to-large effects for the response difference between user and nonuser groups [17,28]. Based on the relevant research and using G*Power 3.1 (Heinrich Heine University Düsseldorf) for a 2 (group: vapers vs nonvapers)×2 (cue condition: social pressure vs no social pressure) mixed design, we powered the study for the group × cue condition interaction (group×cue condition) assuming a medium effect (*f*=0.25; partial η-squared ≈ 0.06; power=0.80). We assumed a within-participant correlation of *r*=0.50 between cue conditions and a nonsphericity correction of *ε*=1.0 (sphericity is not applicable with 2 within-subject levels). This yields a minimum required sample of 34 (n=17 per group). To ensure robustness and account for potential data loss (eg, eye-tracking dropout and physiological artifacts), we plan to recruit 40 participants in total (n=20 vapers and n=20 nonvapers).

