##### Primary Analyses

For the primary aim of examining differences in psychological and physiological responses between vapers and nonvapers during VR cue exposure with and without social pressure, a mixed-model ANOVA will be conducted. Group (vapers vs nonvapers) will serve as the between-subjects factor, and cue condition (social pressure vs no social pressure) as the within-subjects factor. If the assumptions of normality or homogeneity of variance are violated, nonparametric alternatives such as the aligned rank transform ANOVA [55] will be used to preserve the ability to test interaction effects within the mixed design. Follow-up pairwise comparisons will be conducted with Bonferroni-adjusted *P* values.

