### Conclusions

This protocol describes a pilot study that integrates VR with multimodal psychophysiological assessment to examine vaping cue reactivity among young adults. By combining eye-tracking, HR, EDA, and self-report measures within bespoke VR environments, this study aims to establish the feasibility of VR-based biomarkers in distinguishing vaping status and modeling vaping-related intentions and susceptibility. The findings will guide the development and evaluation of scalable, noninvasive VR tools for identifying early markers of nicotine use risk. This work also lays the groundwork for extending and testing the approach with younger adolescents, with the long-term goal of supporting early detection and prevention of nicotine addiction and initiation.

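### The headline objective asks whether VR responses can distinguish vapers from nonvapers, but the primary analysis compares group means and no described analysis estimates discrimination

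*Protocol article*

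**What the plan says.** Three places in the protocol article pose a question about telling vapers and nonvapers apart:

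- Abstract, Objective: whether responses "can distinguish young adults who vape from those who do not".
- Introduction, end of Background: whether "psychophysiological responses to vaping cues in VR can differentiate nicotine vaping status among young adults".
- Discussion, Conclusions: "this study aims to establish the feasibility of VR-based biomarkers in distinguishing vaping status".

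The operative text is worded differently. Under Aims, the article states: "The primary aim is to examine differences in psychological (craving, sense of presence, and social presence) and physiological (eye gaze, HR, and EDA) responses". The comparison is of the two groups, with directional hypotheses about which group responds more strongly. The description of the primary analysis opens "For the primary aim of examining differences in psychological and physiological responses between vapers and nonvapers" and names a mixed ANOVA as the test, with group as the between-subjects factor and cue condition as the within-subjects factor.

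Vaping status is the outcome in one analysis only, the LASSO logistic regression under Secondary Analyses. It is labelled exploratory, cross-validation is mentioned only for choosing the penalty, and the text says the results will point to candidate markers for later confirmation and will not yield a generalizable prediction model.

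**The concern.** The group term of the ANOVA has equal group means as its null hypothesis. Rejecting it shows that the averages differ. It does not show how well a measure separates one person from another, which is what a biomarker of vaping status has to do. The interaction term is further away still: it asks whether the group difference changes between the two scenes.

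As described, the pilot could finish with several significant group effects and no estimate that answers the question in its abstract. A reader could then take a significant mean difference as evidence that a measure identifies vapers, although the same result is compatible with weak separation. This matters because the article says the findings will guide development of VR tools and extension to younger adolescents.

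**Working it through.** **Inputs from the article (Study Design).** 20 vapers and 20 nonvapers planned, 17 per group as the minimum; f = 0.25; power 0.80; correlation 0.50 between the two cue conditions. **Assumptions.** Two-sided alpha 0.05, because none is stated; normal distributions, equal variances, equal group sizes, and the best single cut-off.

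**1. The plan's own figure.** The article says "we powered the study for the group × cue condition interaction" with "partial η-squared ≈ 0.06; power=0.80". For a within-between interaction with m = 2 conditions, λ = f²·N·m/(1 − ρ), with 1 and N − 2 degrees of freedom.
- N = 32: λ = 0.0625 × 32 × 2 / 0.5 = 8.0, power 0.781.
- N = 34: λ = 8.5, power 0.807.
- N = 40: λ = 10.0, power 0.869.

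The stated minimum of 34 reproduces exactly, so the sample size is not in error. It is sized for the interaction, which is not the term closest to the headline question.

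**2. The smallest significant group difference.** On the participant mean over the two scenes, d = t(0.975, 2n − 2) × √(2/n). Under the assumptions above, AUC = Φ(d/√2) and misclassification = Φ(−d/2).

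| n per group | d | AUC | Misclassified |
|---|---|---|---|
| 20 | 0.640 | 0.675 | 37.4% |
| 17 | 0.699 | 0.689 | 36.3% |

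Assigning people to equal-sized groups by chance misclassifies 50%.

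**3. Where misclassification falls to one third.** Setting Φ(−d/2) = 1/3 gives d = 2 × Φ⁻¹(2/3) = 0.861. With 20 per group this has p = 0.0097 and an AUC of 0.729. Significant results with p between about 0.05 and 0.01 therefore go with 37% down to 33% misclassified.

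**4. The planning effect, if carried over to the group contrast.** The article applies f = 0.25 to the interaction, so this is only an illustration.
- Per scene: d = 2f = 0.50, AUC 0.638, 40.1% misclassified.
- On the two-scene mean, whose variance is (1 + 0.50)/2 = 0.75 of a single scene's: d = 0.50/√0.75 = 0.577, AUC 0.658, 38.6% misclassified.

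**5. Precision of an AUC at 20 per group.** By the Hanley-McNeil formula, with A = 0.674, Q₁ = A/(2 − A) = 0.508 and Q₂ = 2A²/(1 + A) = 0.543:

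SE = √{[A(1 − A) + 19(Q₁ − A²) + 19(Q₂ − A²)]/400} = 0.0855

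The 95% interval is 0.674 ± 1.96 × 0.0855, or about 0.51 to 0.84. A just-significant marker is compatible with almost no separation and with good separation.

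**The case against.** The strongest reply is that the operative aim and the test agree. The Primary Aim is worded as differences, its hypotheses are contrasts of group averages, and a mixed ANOVA answers them. This stands: the mismatch lies between the headline wording and the primary analysis, not within the Methods.

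Next, classification has its own analysis, and its claims are restrained. The restraint is proper and deserves credit. But the LASSO is framed as examining association with vaping status, and its cross-validation is described only as tuning, so it does not supply the missing estimate.

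Third, a condensed article may leave performance measures to a fuller document, and the registration is not at hand. That is fair, and the absence of a named AUC would not be a finding on its own. The point rests on what the article does state: its objective, its primary test and its description of the classifier.

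Two stronger readings are tempting and should not be drawn.
- A reader might infer that a marker misclassifying more than a third of people would be reported as distinguishing vapers. The article states no reporting rule, so this would be conjecture.
- A reader might take the one-third figure as general. It applies only to significant markers with d below about 0.86. At d = 0.909, detectable with 80% power at 20 per group, misclassification is 32.5%.

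Finally, the normal model may fit craving poorly, since scores of people who have never vaped could cluster near zero.

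**Conclusion.** The concern holds in a limited form. The abstract, introduction and conclusions ask about distinguishing vaping status. The primary analysis tests mean differences, and the exploratory classifier is not described as estimating discrimination. A significant group effect does not by itself answer the headline objective.

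At 20 per group, a just-significant effect means an AUC of about 0.67 and about 37% misclassified; the misclassification stays above one third up to d of about 0.86. These figures depend on the assumed alpha, normality, equal variances and equal group sizes. The mismatch in wording does not depend on them.

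The documents do not support the further claims that the ANOVA is wrong for the primary aim, that the sample size is miscalculated, or that the authors will overstate their results.

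**What to change.** Keep the mixed ANOVA and describe a significant group effect as a difference in group means. Then do one of the following:

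- For each primary measure, taken as the participant's mean over the two cue scenes, report the AUC for vaper versus nonvaper with a 95% confidence interval. Base any statement that a measure distinguishes vaping status on that estimate and interval, presented as exploratory pilot evidence.
- If no AUC is to be reported, reword the objective and conclusions to ask whether responses differ between the groups.

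A pass-or-fail minimum AUC is not needed in a 40-person pilot.

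The cost is one summary per measure from data already being collected, plus edits to wording. With data from 7 participants as of March 2026, it can be settled before analysis. The downside is wide intervals, about 0.51 to 0.84 for a just-significant marker, so few measures may support strong wording. The groups also contrast use on at least 10 of the past 30 days with never having used, so an AUC from this sample would not by itself validate a detection tool.

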**Methods:**

Bespoke VR scenes were developed with input from a youth advisory board to ensure ecological validity. Forty young adults aged 18 to 21 years (20 vapers and 20 nonvapers) will complete a single laboratory session. Participants will experience 3 VR scenes (neutral baseline, vaping cues without social pressure, and vaping cues with social pressure in counterbalanced order). Eye gaze, heart rate, and electrodermal activity will be recorded continuously. Participants will complete standardized assessments of craving, sense of presence, and social presence in VR after each cue scene, followed by a short interview at the end. Quantitative data will be analyzed using mixed-model ANOVAs, correlation metrics, and exploratory regularized regression analyses to examine relationships between physiological responses, behavioral measures, and vaping status.

**Results:**

The project received institutional review board approval in August 2025 and was registered publicly in the Open Science Framework in November 2025. Development of the VR stimuli was completed in December 2025. Participant recruitment and data collection began in February 2026, and 7 participants have been enrolled as of March 2026.

**Conclusions:**

This protocol outlines a pilot study integrating immersive VR and multimodal biometrics to examine vaping cue reactivity in young adults. The findings will guide the development and evaluation of VR-based psychophysiological tools for identifying early markers of nicotine use risk. This work will also lay the foundation for adapting the approach to younger adolescents to support scalable early detection and prevention of nicotine addiction and initiation.

## Introduction

### Background

Nicotine addiction is a critical public health concern, particularly among youth who are vulnerable to initiation through electronic nicotine delivery systems (ie, vaping or e-cigarettes) [1]. Early exposure to nicotine during adolescence can disrupt neurodevelopment, heighten impulsivity, and increase the risk of long-term dependence [2,3]. Due to the ongoing development of their brain’s reward system, young people are especially sensitive to reward-based learning, making them more susceptible to adopting and maintaining addictive behaviors such as vaping. Vaping exposes individuals to aerosols containing toxic particles and chemicals that impair lung function and trigger inflammation [4]. It also increases the likelihood of transitioning to conventional cigarette smoking, compounding long-term health risks such as cardiovascular disease, chronic respiratory illness, and cancer [5]. Given the continued high rates of vaping among young adults [6,7], there is an urgent need for effective early prevention and detection strategies to mitigate nicotine addiction.

Virtual reality (VR) has emerged as a promising tool to study and treat nicotine addiction [8-13]. It enables the creation of realistic cue environments that replicate real-world triggers for nicotine craving and use under controlled yet ecologically valid conditions. For instance, Bordnick et al [13] assessed people’s cravings when exposed to virtual cigarette smoking–related cues to understand their smoking behaviors. A growing body of work has further explored how to best optimize the design of VR scenarios to maximize craving induction, such as manipulating visual context (eg, adding more nicotine product–related images) [14], sensory integration (eg, introducing olfactory cues) [15], or social pressure components [16-18]. Building on these cue exposure paradigms, research has also explored how VR can support prevention and cessation efforts. Pericot-Valverde et al [12], for instance, applied a paradigm to help participants practice cigarette refusal skills. Additionally, Wiser et al [10] and Borelli et al [19] have demonstrated that interactive VR games can enhance engagement and support vaping prevention and cessation among youth. By leveraging VR-enabled features such as immersive learning, tailored content design, and simulated skills practice, these applications suggest that VR could effectively supplement existing treatment and prevention modalities for nicotine addiction.

A key advantage of VR, as compared to other interactive modalities for assessing substance use risk [20], is its capacity for synchronized tracking of behavioral and physiological responses during immersive cue exposure. Existing research has shown that nicotine-related cues, whether physical (eg, cigarette packaging) or virtual (eg, images or videos), can elicit stronger emotional and behavioral responses in cigarette smokers than in nonsmokers [21,22]. Metrics such as attentional bias (measured via eye tracking) and autonomic arousal (eg, heart rate [HR] and electrodermal activity [EDA]) capture implicit and automatic processes that may reveal cue reactivity, substance use tendencies, and motivation to consume nicotine [23]. These biometric responses may address important limitations of existing measures of risk, as most rely on self-report, are prone to social desirability and recall bias, and have limited sensitivity to real-time emotional and cognitive processes underlying addiction [8,24]. Furthermore, VR-elicited biometrics may provide an alternative to biological specimens by serving as noninvasive biomarkers for vaping and nicotine use [25]. Together, VR-based psychophysiological methods may serve as valid and acceptable objective tools for identifying nicotine use and predicting addiction risk.

However, despite the use of VR to study cigarette smoking cue reactivity, little work has examined whether VR can distinguish current and future nicotine vaping behaviors. To date, studies have largely used cigarette smoking cue environments to differentiate individuals based on psychophysiological responses using single modalities such as electroencephalogram and eye-tracking [17,26]. Furthermore, no current work has combined multimodal physiological data (eg, visual attention and physiological arousal) with psychological measures (eg, impulsivity, craving, and motivation to quit) to model individuals’ intentions to initiate or cease vaping. Such predictive modeling could play a crucial and timely role in identifying at-risk individuals early and tailoring interventions accordingly.

This study addresses these critical gaps by evaluating whether psychophysiological responses to vaping cues in VR can differentiate nicotine vaping status among young adults. It also explores the associations between biometric reactivity, nicotine vaping status and intention, and individuals’ addiction-related traits (eg, impulsivity and emotion regulation). The long-term goal is to inform the development of real-time adaptive systems capable of detecting and predicting vaping-related intentions, addiction, and initiation risk in naturalistic VR settings, and delivering tailored behavioral-change interventions. This will support the development of early, personalized prevention strategies to enhance health outcomes among youth.

### Aims

#### Overview

The overall goal of this study is to evaluate the feasibility of VR-based psychophysiological assessment methods as an early detection and risk prediction tool for nicotine addiction. This paper presents a mixed methods experimental study protocol designed to examine how psychophysiological responses to vaping cues in VR differ among young adults based on their nicotine vaping status and intentions. The study integrates psychological, physiological, and qualitative measures across 2 bespoke VR cue exposure scenes. Participants include two groups: (1) young adults who currently vape (vapers), for assessment of nicotine dependence and quit intentions; and (2) individuals who have never vaped (nonvapers), for evaluation of susceptibility to initiation.

#### Primary Aim

The primary aim is to examine differences in psychological (craving, sense of presence, and social presence) and physiological (eye gaze, HR, and EDA) responses between young adults who currently vape and those who have never vaped during exposure to VR vaping cues presented with and without social pressure. We hypothesize that vapers will exhibit stronger craving, a greater sense of presence and social presence, increased visual attention to vaping cues, and heightened physiological arousal compared with nonvapers across both VR scenes. We further expect that both groups will show stronger psychological and physiological responses in the social pressure condition than in the no pressure condition.

#### Secondary Aim

The secondary aim is to assess correlations between multimodal physiological measures (eye tracking, HR, and EDA) and subjective vaping-related outcomes, including craving, sense of presence, social presence, nicotine dependence, and quitting intention (among vapers), as well as susceptibility to initiate vaping (among nonvapers). We hypothesize that psychophysiological responses during VR cue exposure will be significantly associated with subjective vaping-related measures, such that greater attentional and autonomic reactivity will correlate with higher craving, dependence, and quit intention among vapers, and with higher susceptibility to initiate vaping among nonvapers. As an exploratory analysis, we will further examine whether combinations of physiological and subjective measures predict vaping status (vaper vs nonvaper).

#### Qualitative Aim

Following the experimental section, participants will complete a brief semistructured interview to understand their perceptions of the VR scenes, their awareness of vaping cues, and their cognitive, affective, and physiological responses to the cues. These qualitative insights will contextualize the study’s quantitative findings and inform the feasibility and acceptability of the VR scenarios for vaping behavior assessment and intervention.

